## Abstract

**Background:**

An increasing number of falls result in an emergency call and the subsequent dispatch of paramedics. In the absence of physical injury, abnormal physiological parameters or change in usual functional status, it could be argued that routine conveyance by ambulance to the Emergency Department (ED) is not the most effective or efficient use of resources. Further, it is likely that non-conveyed older fallers have the potential to benefit from timely access to fall risk assessment and intervention. The aim of this randomised controlled trial is to evaluate the effect of a timely and tailored falls assessment and management intervention on the number of subsequent falls and fall-related injuries for non-conveyed older fallers.

**Methods:**

Community dwelling people aged 65 years or older who are not conveyed to the ED following a fall will be eligible to be visited at home by a research physiotherapist. Consenting participants will receive individualised intervention strategies based on risk factors identified at baseline. All pre-test measures will be assessed prior to randomisation. Post-test measures will be undertaken by a researcher blinded to group allocation 6 months post-baseline. Participants in the intervention group will receive individualised pro-active fall prevention strategies from the clinical researcher to ensure that risk factors are addressed adequately and interventions carried out. The primary outcome measure will be the number of falls recorded by a falls diary over a 12 month period. Secondary outcome measures assessed six months after baseline will include the subsequent use of medical and emergency services and uptake of recommendations. Data will be analysed using the intention-to-treat principle.

**Discussion:**

As there is currently little evidence regarding the effectiveness or feasibility of alternate models of care following ambulance non-conveyance of older fallers, there is a need to explore assessment and intervention programs to help reduce subsequent falls, related injuries and subsequent use of health care services. By linking existing services rather than setting up new services, this pragmatic trial aims to utilise the health care system in an efficient and timely manner.

**Trial registration:**

Australian New Zealand Clinical Trials Registry: ACTRN 12611000503921

## Background

More than 40 percent of people aged 65 years or older experience one or more falls each year, often resulting in injuries [1,2]. Consequences of falls include a reduction in physical activity and functional decline which in turn can lead to a poorer quality of life and social isolation. All these factors increase the risk of dependency and institutionalisation [3-5].

Many older people do not seek medical attention after a fall [6] but a significant and increasing number require paramedic attendance as a consequence of a fall. In the period July 2008 – June 2009, the Ambulance Service of New South Wales (ASNSW), Australia attended to 42,331 fallers aged 65 years and older which constitutes approximately 5.1% of all emergency ambulance responses [7]. This proportion is similar to the 7.5% reported in an urban Emergency Medical Service system in the USA [8]. The demand for emergency services to assist older fallers is likely to increase with population ageing.

In most countries, the current practice for ambulance service paramedics is to convey older people who fall to the hospital Emergency Department (ED) unless the person refuses or declines transport. Fallers account for almost one fifth of ED presentations by older adults [1,9] and in the absence of physical injury, abnormal physiological parameters or change in usual functional status, it could be argued that routine conveyance by ambulance to the ED is not the most effective or efficient use of resources. Furthermore, ED personnel face significant time constraints and therefore focus on addressing the immediate consequences of a fall which leaves little scope for considering a person’s risk of future falls and the provision of appropriate prevention strategies.

Currently the ASNSW has a 25% non-conveyance rate for older fallers which is similar to that reported by ambulance services in other countries [34% in the United Kingdom (UK) [10], 40% in the United States of America [8]. A number of articles have described non-conveyance to be due to the treatment on scene being “sufficient” or the person requiring “lift assist only” [10-14]. What happens to these older fallers subsequent to the acute event is unclear, although a study from the UK highlighted substantial unplanned healthcare contact within two weeks, with 47% of these people calling the ambulance service again and 24% presenting to an Emergency Department [15]. An independent clinical review of these cases demonstrated that paramedics were almost certainly making correct decisions about conveyance at the time of assessment, but functional declines as a result of the fall frequently occurred 1–2 days later [15]. A recently completed study in New South Wales, Australia has also highlighted the high-risk nature of non-conveyed older fallers, demonstrating that within a 6 month follow-up period 58% of people fell again, 40% sustained a fall-related injury and 27% called an ambulance again due to a fall [16].

Rapid referral and timely access to alternate services to ED was identified as a gap in service provision in the UK based study and there is now evidence that an individualised multifactorial fall prevention program provided by community falls teams has significant benefits for non-conveyed older fallers [17]. This approach to intervention is consistent with the UK clinical fall guidelines [18] and included strength and balance training, assessment and modification of home hazards and medication review. The intervention group experienced significantly fewer falls (incidence rate ratio 0.45, 95% confidence interval (CI) 0.35 to 0.58) and the time to first subsequent fall was also significantly longer (median difference 145 days, HR 0.32, 95% CI 0.23 to 0.44). Furthermore, the intervention group made significantly fewer emergency calls for ambulance services within the follow-up period, compared to the control group participants who received standard emergency care (IRR 0.60, 95% CI 0.40 to 0.92).

Older fallers who require ambulance care in NSW appear to be comparable to their counterparts in the UK regarding level of fall risk, so it is likely that non-conveyed older fallers living in NSW also have the potential to benefit from timely access to fall risk assessment and intervention. The aim of this randomised controlled trial is to evaluate the effect of a rapid, timely and tailored intervention in older people who are not conveyed to a hospital ED following a fall.

The impact of the project will be evaluated over 12 months using a) rate of falls and fall-related injury, b) use of Ambulance resources, c) use of ED and in-patient services, d) incremental costs (or cost savings) of implementing this targeted approach, e) impact on the health care system (i.e. post acute care services (PACS) or Home Medication Review (HMR) services, etc.), f) uptake and adherence to recommendations and g) the benefits beyond fall prevention i.e. improved level of function and better quality of life. Importantly, rather than setting up a new service, our intervention will involve expanding existing services where possible, such as PACS which are capable of rapid responses to the urgent needs of community dwelling older people [19,20].

## Methods

### Design

A single blind randomised controlled trial will be conducted to evaluate the impact of rapid access to a comprehensive assessment and intervention program offered to non-conveyed older fallers. Subsequent falls and fall-related injuries, ambulance service use, ED and in-patient service use, incremental costs (or cost savings) of implementing this targeted approach, and impact on the health care system will be evaluated. In addition, we will investigate uptake and adherence to recommendations and benefits of the intervention beyond fall prevention.

### Participant selection and identification

Community dwelling people aged 65 years or older who receive ambulance care as a result of a fall and who are considered to be appropriate (or choose) to be left at home will be invited to participate in the trial. People living in Residential Aged Care Facilities will be excluded. People living at home with a known diagnosis of dementia and no carer will also be excluded as well as those who are unable to speak and understand sufficient English to participate fully in the trial.

All referred non-conveyed older fallers will be contacted via telephone to establish that there has been no acute deterioration in their health or level of function following the fall. For falls that occur between Monday and Thursday, calls will be made within 24 hours. For falls that occur between Friday and Sunday, calls will be made on the following Monday. Once it is established that there is no requirement for emergency care, the older person will be invited to participate in a fall prevention program. If verbal consent to participation is gained then an appointment for a home visit will be offered as soon as possible.

Ethics approval has been obtained from Sydney Local Health Network Ethics Review Committee (Royal Prince Alfred Hospital Zone- Protocol No X10-0352 & HREC/10/RPAH/616) and written consent will be obtained from all eligible participants.

### Ambulance station and paramedic participation

The participating ambulance stations will be located in the eastern suburbs of Sydney, Australia and are largely within the Prince of Wales Hospital Post-Acute Care (POWH PACS) service catchment area (Randwick, Australia). All paramedics working at the participating stations will receive education with respect to the rationale for the study and will be trained in the process used to refer potentially eligible patients. Paramedic assessment will reflect existing standard practice within the ambulance service, which for this patient population is underpinned by an algorithmic clinical protocol (Protocol T19 – Falls in the elderly). This protocol provides decision making support for paramedics when determining whether patients require transport to hospital. If medically appropriate, as determined by the outcome of the algorithm, paramedics can recommend non-conveyance to older fallers. Patients are able to refuse or decline transport despite a recommendation for conveyance on the understanding they are able to give informed consent. When an older person is not conveyed to hospital, the paramedic will inform him/her that the Ambulance Service officer will contact them within 24 hours (72 hours if attended on a Friday). Should the person require care before then, they will be advised, as is current practice, to contact their local General Practitioner (GP) or call an ambulance if they feel this is required. The paramedics will then contact the study coordinator (via mobile phone with voicemail) to provide the contact details of the eligible older person they treated (Figure 1).

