### Sample size

The primary outcome measure will be the proportion of participants who fall during the twelve month follow-up period. Based on the fall rate from similar work in the field we estimate the fall rate in the control arm of this study will be 60%. We further estimate that the intervention will reduce the number of fallers by 33% in this period – a conservative estimate given the 55% reduction in fall rates reported in the UK over 1 year for a study with a similar intervention [37]. Consequently, accounting for dropouts (10%), a power of 90% and a 5% significance level, a total sample size of 234 is required. Based on our previous studies, a sample of 234 will also be adequate for determining clinically significant differences between the groups for our continuously scored measures [38], and for developing multivariate models pertaining to uptake and adherence [39].

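### Patients attended on a Saturday are told to expect contact within 24 hours, but their call is scheduled for Monday

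*Protocol article*

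**What the plan says.** Two adjacent Methods sections of the Protocol article give a time for the first contact after a fall.

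- **What the patient is told** (Ambulance station and paramedic participation): "the Ambulance Service officer will contact them within 24 hours (72 hours if attended on a Friday"). The 24-hour time is the rule and Friday is the one exception. The advice for the interval follows directly: "Should the person require care before then, they will be advised, as is current practice, to contact their local General Practitioner (GP"). An ambulance call is the other route offered.
- **When calls are made** (Participant selection and identification): for the first four days of the week the schedule matches the message, as "For falls that occur between Monday and Thursday, calls will be made within 24 hours". The remaining three days share a different rule: "For falls that occur between Friday and Sunday, calls will be made on the following Monday".

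The second section also gives the purpose of the call. Referred people are "contacted via telephone to establish that there has been no acute deterioration in their health or level of function following the fall". The invitation to take part comes only after that check.

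**The concern.** The call schedule treats Friday, Saturday and Sunday alike, whereas the message to the patient makes an exception for Friday only. A person attended on Saturday is therefore told 24 hours, although the schedule has no call before Monday.

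What is at stake is patient information, not inference. The call is a check for deterioration as well as a recruitment step, and the advice on seeking care is framed around the time before it. Someone who worsens on Sunday and believes a call is due that day might wait for it. The article's own Background gives this some weight: it cites a UK review in which functional decline often appeared one to two days after the fall, which for a Saturday fall means Sunday or Monday.

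**Working it through.** The plan gives no figure to reproduce. The check is clock arithmetic on the two stated schedules.

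**Inputs**
- Time told to the patient: 24 hours, or 72 hours for a Friday attendance (Ambulance station and paramedic participation).
- Call day for falls from Friday to Sunday: the following Monday (Participant selection and identification).
- Planned sample: "a total sample size of 234 is required" (Sample size).
- The article gives no calling hours, so the main result lets the call come at any hour on Monday.

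**Notation.** Let t be the hour of attendance on the day concerned and c the hour of the call on Monday, each from 0 up to but not including 24. The fall and the attendance are taken to be on the same day.

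**Saturday**
- Wait = 48 − t + c.
- Shortest: t close to 24 and c = 0 gives just over 24 hours.
- Longest: t = 0 and c close to 24 gives just under 72 hours.
- Overrun = wait − 24 = 24 − t + c. As t is below 24, this is above zero for every t and c. It runs from just over 0 to just under 48 hours.

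No hour on Monday meets the 24 hours.

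**Friday and Sunday, for comparison**
- Sunday: wait = 24 − t + c, which is at most 24 only if c ≤ t.
- Friday: wait = 72 − t + c, which is at most 72 only if c ≤ t.

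On both days the stated time can be met, provided the Monday call comes no later in the day than the attendance did. They are not counted as contradictions.

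**With calls between 09:00 and 17:00 (assumed)**

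| Day attended | Time told (h) | Wait to Monday call (h) |
|---|---|---|
| Friday | 72 | about 57 to 89 |
| Saturday | 24 | about 33 to 65 |
| Sunday | 24 | about 9 to 41 |

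The Saturday result does not depend on these hours. They only narrow the range.

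**How many people**

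The article gives no distribution of falls by weekday.
- Even spread (assumed): 1/7 = 14.3%, and 234 × 1/7 = 33.4, about 33.
- Saturday share of 10% (assumed): 234 × 0.10 = 23.4, about 23.
- Saturday share of 20% (assumed): 234 × 0.20 = 46.8, about 47.

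**The case against.** The strongest reply is that the two sections may not describe the same contact. One names an Ambulance Service officer, the other names no caller, and the referral itself goes to the study coordinator. The recruitment figure, which might settle who calls, is not shown. This carries little weight: the article describes only one telephone contact after the fall, and Friday plus 72 hours falls on Monday, the day the call schedule gives.

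A second reply is that Friday is shorthand for the weekend and that training material would hold the exact script. That is possible, but the text does not say so, and the neighbouring section writes out Friday to Sunday when it means all three days. If shorthand was intended, the correction simply makes the meaning explicit.

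Three points do stand:
- The risk that a patient waits for the call is conjecture. Every patient is still told to use a GP or ambulance if care is needed.
- The call comes before consent, baseline assessment and randomisation, so it cannot differ between arms or affect the outcome, the analysis or the sample size.
- The 234 are people who will have been called and will have agreed to take part, whereas the message goes to non-conveyed fallers more widely. Their number is not given, so the counts only illustrate scale.

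**Conclusion.** The concern holds, as a low-priority error in what patients are told. The contradiction itself rests on one reading, that both sections describe the same call, and needs no assumption about calling hours or the spread of falls over the week. The counts of 33, or 23 to 47, depend wholly on the assumed Saturday share, and the conclusion does not need them.

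**What to change.** Change the sentence in Ambulance station and paramedic participation so that the paramedic gives the times in the call schedule: contact within 24 hours for people attended Monday to Thursday, and on the following Monday for those attended Friday to Sunday. The advice for the interval then refers to a correct time.

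Naming Monday is better than extending the 72-hour limit to the whole weekend, because a person attended early on Friday and called later in the day on Monday waits more than 72 hours.

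The message is the part to correct, because an exception for Friday makes sense only if no weekend calls are made. The cost is one sentence in the protocol, repeated in the paramedics' training, with no extra calls or staff and no change in call timing. Should the sponsor in fact intend Saturday patients to be reached within 24 hours, the call schedule would have to change instead, and weekend calls would be needed.

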**Figure 1 F1:**
[figure not shown]
**Study outline; recruitment process and assessment.** Legend Figure 1: T19: Decision making protocol for paramedics when assessing falls in the elderly; ED: Emergency department; Hx: History; ICON FES: Iconographic falls efficacy scale; GDS: Geriatric depression scale; EQ-5D: Euro-Qol health questionnaire; IPEQ: Incidental and planned exercise questionnaire; GP COG: The General Practitioner assessment of Cognition; PACS: Post Acute Care Service; HMR: Home medication review; GP: General Practitioner.

### Measurement and procedures

All eligible older fallers will be visited at home by a research physiotherapist. The program will be explained in detail to participants and written consent will be obtained prior to undertaking the baseline assessment. All participants will undergo two measurements: one on entry to the study (baseline assessment) and one after the 6-month intervention period. Table 1 highlights the measures to be undertaken. At the end of the baseline assessment, the researcher will generate a list of risk factors identified and written suggestions about how they might be addressed using a template with capacity for free text to individualise advice. All pre-test measures will be assessed prior to randomisation. Post-intervention period measures will be undertaken by personnel blinded to group allocation.

**Table 1 T1:** List of measures to be collected at baseline assessment (BA) and at reassessment (RA)

	**BA**	**RA**	**O**
**Socio-demographics**			
Age, gender, education, occupation, place and type of residence and number of co-habitants.	✓	**✗**	**✗**
**General health and function**			
Detailed information regarding non-transported fall.	✓	**✗**	**✗**
Information regarding falls and fractures in previous 12 months.	✓	**✗**	**✗**
Ambulance service use and hospitalisation in last 12 months (in general, and due to falls).	✓	**✗**	**✗**
Disease history of previous 12 months (Multipurpose Australian Co-morbidity Scoring Scale (MACSS)).	✓	**✗**	**✗**
Medication use.	✓	✓	**S**
Assistive walking device (indoor and outdoor use), need for assistance when performing seven Instrumental Activities of Daily Living (IADL).	✓	✓	**S**
The Incidental and Planned Exercise Questionnaire (IPEQ) will provide estimates of the frequency and duration of planned and incidental exercise [21].	✓	✓	**S**
Self-reported fear of falling and balance ability on a 5-point Likert-scale.	✓	✓	**S**
**Quality of life**			
The EuroQol-5D is a widely used utility-based quality of life instrument for estimating Quality Adjusted Life Years (QALYs) for economic evaluations [22]. It provides a simple descriptive profile and a single index value for health related quality of life.	✓	✓	**S**
**Neuropsychological**			
Fear of falling will be assessed using the Iconographical Falls Efficacy Scale-Short version (ICON FES) [23].	✓	✓	**S**
The 15-item Geriatric Depression Scale (GDS) will assess symptoms of depression [24,25].	✓	✓	**S**
General Practitioner assessment of COGnition (GPCOG) will provide a global measure of cognition [26] The GPCOG is a reliable, valid and efficient tool to quickly screen for dementia, which has been shown not to be influenced by the cultural or linguistic background of the person being assessed.	✓	✓	**S**
Executive Function (working memory, set shifting and response inhibition) will be assessed using the Trail-Making Test A and B (TMT A/B ) [27,28].	✓	✓	**S**
**Physical**			
Objective measure of falls risk using the QuickScreen [29]. This is a multifactorial, reliable and externally validated falls risk assessment tool. It is able to predict future fall risk with an accuracy of 72%.	✓	✓	**S**
Timed up and Go [30] and the co-ordinated stability test [31].	✓	✓	**S**
**Home environment**			
The HOME FAST assessment score is a valid predictor of falls, with an increased risk of 1-2% for every additional point scored on the scale [32].	✓	✓	**S**
**Follow-up- 12 months**			
Falls (monthly diaries) [33].			**P**
Subsequent use of health services (differentiation between fall-related or other medical reason) collected from monthly diary and with further telephone call for clarification if required.			**S**
GP visit, Specialist medical practitioners visit, ambulance service use, ED presentation, hospital admission, physiotherapy, occupational therapy.			
Number of falls requiring ED attendance and/or hospitalisation collected from monthly diary and with further telephone call for clarification if required.			**S**
Use of NSW Ambulance Service, including time on scene (routinely collected Ambulance Service data).			**S**
Any ED presentation or hospitalisation including Diagnosis Related Group (DRG) and Length of Stay (LOS) data (measured using falls calendar data and corroborated through the NSW Admitted Patient Data Collection).			**S**
Use of any community health services – GP visits, Home medication review (HMR), Aged Care Assessment Team (ACAT) referrals, use of Post Acute Care Service (PACS) services etc. (measured using monthly falls calendar data).			**S**
Uptake and adherence to recommendations (based on initial and post-intervention assessments).	**✗**	✓	**S**

*BA* Baseline Assessment, *RA* Reassessment, *O* Outcome measure, *S* secondary, *P *Primary.

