### Economic analysis

Analysis will be undertaken in the manner used in previous fall prevention studies led by Campbell and Robertson [35,36]. The study will collect data on the cost to deliver the assessment and intervention package (including staff costs, training, capital costs and consumables), in-patient hospital admissions, ED presentations and other health and community service contact, fall rates and utility-based quality of life. Data linkage of all trial participants via CHeReL (Centre for Health Record Linkage) will be used to estimate the resource use associated with inpatient and ED visits. Incremental cost-effectiveness ratios will be calculated in terms of a) the incremental cost per fall prevented, b) the incremental cost per triple zero call avoided, c) the incremental cost per ED presentation avoided, and d) the incremental cost per hospital admission avoided and e) the incremental cost per QALY gained. Using the mean costs in the intervention and control arms, and the mean health outcomes in the control and intervention groups, the incremental cost per additional health outcome gained (outcomes a-e above) of the intervention group compared to control group will be calculated; results will be plotted on a cost-effectiveness plane. Bootstrapping will be used to estimate a distribution around costs and health outcomes and to calculate the confidence intervals around the incremental cost-effectiveness ratio. One way sensitivity analysis will be conducted around key variables, and a probabilistic sensitivity analysis will be conducted to estimate the joint uncertainty in all parameters; a cost-effectiveness acceptability curve (CEAC) will be plotted. A CEAC provides information about the probability that an intervention is cost-effective, given a decision maker’s willingness to pay for each additional health outcome.

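### ED presentations that do not end in admission rest on participants' calendars with no stated record check, although the same protocol plans linkage of ED records for its economic analysis

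*Protocol article*

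**What the plan says.** The 12-month follow-up block of Table 1 lists as a secondary outcome "Any ED presentation or hospitalisation including Diagnosis Related Group (DRG) and Length of Stay (LOS) data", which is to be "measured using falls calendar data and corroborated through the NSW Admitted Patient Data Collection". No ED record source is named in that row.

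Two neighbouring rows touch the same events. One covers health service use in general, including ED presentations and admissions, taken from the monthly diary with a clarifying call where needed. The other is "Number of falls requiring ED attendance and/or hospitalisation collected from monthly diary and with further telephone call for clarification if required". Ambulance use, by contrast, is taken from the ambulance service's routine data.

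The Economic analysis section plans linkage of all trial participants through the state record linkage centre. The linkage "will be used to estimate the resource use associated with inpatient and ED visits". One of the ratios to be reported there is "the incremental cost per ED presentation avoided".

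On blinding, the Design section says "A single blind randomised controlled trial will be conducted", and Measurement and procedures says "Post-intervention period measures will be undertaken by personnel blinded to group allocation". Under Intervention group, a clinical researcher works actively with the participant to put the recommendations into practice. Under Control group, participants get a written list of their risk factors and no further support.

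**The concern.** The row claims to cover every ED presentation, but the check it names is by its title a collection of admitted patients. ED visits without admission are left to self-report alone.

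That would matter less if participants were blinded or if no better source were in reach. Neither holds. The arms differ in ways participants can see, and the same protocol plans linkage that covers ED visits. As written, the diary feeds the outcome comparison and linked records feed resource use. The protocol does not say which count forms the denominator of the cost per ED presentation avoided.

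Two things are at stake. The between-arm comparison of ED use could be distorted in either direction. The clinical and economic results could also report different numbers of ED presentations for the same participants.

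**Working it through.** The protocol states no figure on this point, so there is none to reproduce. The check sets the sections side by side and then illustrates the possible size.

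**Source by event type**

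| Event | Source in Table 1 | Record check named in Table 1 | Covered by linkage in Economic analysis |
|---|---|---|---|
| ED visit ending in admission | Calendar | Admitted-patient collection | Yes |
| Other hospital admission | Calendar | Admitted-patient collection | Yes |
| ED visit ending in discharge home | Calendar | None | Yes (ED visits) |

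The gap is in the last line only.

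**Can reporting differ by arm?** The protocol never says in words that participants are unblinded. It follows from three statements: the trial is single blind, the blinding described is that of the personnel taking post-intervention measures, and one arm gets active support while the other gets a written list.

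**Illustration of size (assumed inputs).** Let *c_I* and *c_C* be the shares of ED visits that diaries capture in the intervention and control arms. If the true rate ratio is 1.0 and no visit is recovered from records, the apparent ratio is *c_I* / *c_C*.

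- 90% against 80%: 0.90 / 0.80 = 1.125. Reversed: 0.80 / 0.90 = 0.89.
- 90% against 70%: 0.90 / 0.70 = 1.29. Reversed: 0.70 / 0.90 = 0.78.

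These figures ignore the check on admitted visits. Suppose instead that the admitted-patient collection recovers every ED visit that ends in admission, and that a share *u* of ED visits does not end in admission. The apparent ratio is then

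(1 − u + u·c_I) / (1 − u + u·c_C).

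The documents do not give *u*. With assumed values:

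| u | 90% vs 80% | 80% vs 90% | 90% vs 70% | 70% vs 90% |
|---|---|---|---|---|
| 0.3 | 0.97/0.94 = 1.03 | 0.94/0.97 = 0.97 | 0.97/0.91 = 1.07 | 0.91/0.97 = 0.94 |
| 0.5 | 0.95/0.90 = 1.06 | 0.90/0.95 = 0.95 | 0.95/0.85 = 1.12 | 0.85/0.95 = 0.89 |
| 0.7 | 0.93/0.86 = 1.08 | 0.86/0.93 = 0.92 | 0.93/0.79 = 1.18 | 0.79/0.93 = 0.85 |

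Column heads give intervention against control. If corroboration only confirms visits already on the calendar and adds none, the unadjusted figures apply.

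**Effect on the cost ratio.** Let *m* be the true mean number of ED presentations per participant, equal in both arms. Complete records would show m − m = 0 presentations avoided. Diaries capturing 90% in controls and 80% in the intervention arm, with no recovery from records, would show 0.90m − 0.80m = 0.10m avoided. The choice of count therefore decides whether the denominator is zero or positive in this example.

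**The case against.** The strongest reply is that a diary corroborated by records is a recognised design, and that the diary is needed anyway to separate fall-related events from others. The Economic analysis section does not say that the linked data are for costing alone, and nothing bars their use for the Table 1 outcome. Which dataset feeds which table, and how conflicts are settled, is the kind of detail an article leaves to the full protocol or analysis plan. Diary identification with linked costing is not a contradiction in itself. This is also one row among many secondary outcomes.

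Much of this stands. The diary has a necessary role, and the two sections do not formally contradict each other. But the source and the check in this row are stated choices, not omitted detail, and the stated check does not reach ED visits without admission.

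Several stronger readings are tempting and are not supported:

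- *That admissions are equally exposed.* For admissions, DRG and length of stay, an admitted-patient collection is a suitable check. A DRG would in practice come from records in any case.
- *That only the intervention arm has regular contact with trial staff.* The Discussion promises regular contact with all participants, and Outcome measures provides telephone follow-up of unreturned calendars. The asymmetry lies in the support given, not in contact as such.
- *That the 10% dropout allowance implies about 23 of 234 participants (0.10 × 234 = 23.4) with truncated diaries but complete linked records.* The 10% is a sample-size allowance, and no section says that linkage continues after withdrawal.
- *That the linkage is already done or paid for.* It is planned, and nothing shown mentions its funding.

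**Conclusion.** The point holds in a limited form. ED presentations not followed by admission have no stated record check in Table 1, participants can see their allocation, and ED linkage for all participants appears in the protocol only under resource use. The ED outcome and the cost per ED presentation avoided could therefore rest on different counts.

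The documents show a risk of bias, not its presence, direction or size. The range from 0.78 to 1.29 rests on assumed capture of 70% to 90% and on no recovery of admitted visits from records. With full recovery of those visits and 30% to 70% of ED visits not admitted, the same capture range gives at most 0.85 to 1.18. That the linked ED records are more complete than the diary is likewise an assumption, since their coverage is not described.

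The primary falls outcome is not affected. The point is worth correcting because ED use is a named evaluation aim and an economic denominator.

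**What to change.** In the Table 1 row on ED presentations and hospitalisations, name the linked ED and inpatient records planned under Economic analysis as the source for ED presentations and admissions, with DRG and length of stay from the inpatient records. State that the same counts serve the outcome comparison and the economic ratios. Keep the diary and clarification calls for two purposes: classifying events as fall-related, and adding events outside the linked data. Have the neighbouring diary-based rows refer to the same set of events.

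The cost is mainly wording, since the linkage is already planned and the trial already uses routine data for ambulance use. Results for this outcome would wait for linkage. Before the source is fixed, the coverage of the linked ED data must be confirmed.
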